**Fig. 1 Fig1:**
[figure not shown]
Flow chart of the CIAP study. *An* aneurysm, *RA* ruptured aneurysm, *UIA* unruptured intracranial aneurysm

### Design

Individuals in the UIA follow-up cohort will be allocated to two groups, a modeling and a validation group, in a ratio of 2:1. Taking the annual rupture rate as 1% [2], the rate of loss would be less than 20%. The data will be analyzed statistically in the 5th years, the expectation being that at least 130 patients’ aneurysms will rupture in the first 4 years. The modeling group will be used to establish the risk of UIA rupture and compare relevant clinical information, radiological images, hemodynamic variables, genetic factors, HRMRI findings, and biomarkers [12, 13, 26–37] between the rupture and non-rupture groups to identify the risk factors for rupture. These will then be incorporated into a multi-dimensional model for predicting risk of UIA rupture. The validation group will then be used to validate that model (Fig. 2).

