**Methods:**

The China Intracranial Aneurysm Project-2 (CIAP-2) will comprise screening of a cohort of 500 patients with UIA (From CIAP-1) and focus on hemodynamic factors, high resolution magnetic resonance imaging (HRMRI) findings, genetic factors, and biomarkers. Possible risk factors for rupture of UIA, including genetic factors, biomarkers, HRMRI, and hemodynamic factors, will be analyzed. The first project of the China Intracranial Aneurysm Project (CIAP-1; chaired by the Department of Neurosurgery, Tangdu Hospital, Fourth Military Medical University, Xi’an, Shaanxi, China) will prospectively collect a cohort of 5000 patients with UIA from 20 centers in China, and collect baseline information for each patient. Multidimensional data will be acquired in follow-up assessments. Statistically significant clinical features in the UIA cohort will also be analyzed and integrated into the model for predicting risk of UIA rupture. After the model has been set up, the resultant evidence-based prediction will provide a preliminary theoretical basis for treating aneurysms at high risk of rupture.

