### Model building (first set of UIA queues)

The following possible or established risk factors for UIA will be collected and analyzed: age; sex; blood pressure, smoking, alcohol consumption, hyperlipidemia, diabetes mellitus, and family history of subarachnoid hemorrhage, intracranial aneurysm, and autosomal dominant diseases (polycystic kidney, Marfan syndrome, collagen dysplasia, etc.)The following imaging data will be collected and analyzed: shape, location, size, aspect ratio and odds ratio of aneurysms, morphological factors such as the angle of the aneurysm jet, and known risk factors for rupture.In our experience, follow-up angiography alone does not adequately predict the outcome whereas HRMRI is a more useful means of following these lesions [38]. We have also found and reported that aneurysm wall enhancement on HRMRI predicts instability of an intracranial aneurysm [39]. HRMRI will be performed on patients enrolled in the UIA follow-up cohort at the 20 participating centers and HRMRI-identified aneurysm wall enhancement assessed as a possible predictor of UIA rupture. Two-dimensional short-axis images of the aneurysms generated from the registered pre-and post-contrast T1w-SPACE images will be used to identify wall enhancement [13].To identify risk factors, the nested cohort study will incorporate the following: incidence of aneurysm rupture in the follow-up cohort, the definition of UIA recently rupture before the duration of follow-up was high risk of rupture of UIA, acquisition of imaging data for hemodynamic calculations; according to the aneurysm ratio of 1:2 UIA (rupture vs non-rupture), and analysis of differences in hemodynamic variables, genetic factors, and biomarkers.A.Analysis of hemodynamic variables: A three-dimensional shape will be created and image data from computed tomographic angiography, magnetic resonance angiography, or DSA saved as DICOM files. Once the 3D model has been reconstructed, it will be saved in an STL file format. A rigid wall in the parent vessel and aneurysm will be assumed in the simulation of hemodynamics. We will start by using ANSYS ICEM CFD (Materialise, Leuven, Belgium) to build a finite element model, then perform a simulation on ANSYS CFX software (Materialise), and finally use ANSYS CFX POST postprocessing to calculate Wall Shear Stress (WSS), maximum wall shear stress (WSSmax), low WSS areas, steady state of blood flow, and so on. Our team has already identified that these factors are associated with the stability of aneurysms [40–42].B.Gene and biomarker analysis: Blood samples will be collected from all participants and specimens of the aneurysm wall from patients who undergo craniotomy. Target chromosomes will be tested for blindly. Target genes and biomarkers identified as possibly relevant by the latest international research will be tested. Differences in genes and biomarkers between rupture and non-rupture groups will be compared to identify rupture-related factors.

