### Statistical analysis methods

#### Statistical analysis of clinical data

Continuous variables will be expressed as mean and standard deviation analyzed by one-way anova. Categorical variables will be expressed as quantity (rate) and compared using χ^2^ tests. Continuous variables that are not normally distributed will be expressed as medians and quantile intervals and compared using the Mann–Whitney nonparametric test. P < 0.05 will denote a significant difference.

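### Factors enter the prediction model because they differ significantly between rupture and non-rupture groups, which with about 5 to 6 events per named candidate tends to inflate effects and make predicted risks too extreme

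*Protocol article*

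**What the plan says.** The route into the model is described in several places in the protocol article.

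- **Design:** clinical, imaging, hemodynamic, genetic, HRMRI and biomarker variables are compared between the two outcome groups to find risk factors, and of the factors so found it says: "These will then be incorporated into a multi-dimensional model for predicting risk of UIA rupture".
- **Abstract, Methods:** "Statistically significant clinical features in the UIA cohort will also be analyzed and integrated into the model".
- **Model building:** the clinical candidates are "age; sex; blood pressure, smoking, alcohol consumption, hyperlipidemia, diabetes mellitus, and family history of subarachnoid hemorrhage, intracranial aneurysm, and autosomal dominant diseases". Imaging, wall-enhancement and hemodynamic lists follow, and the last is left open. For the molecular factors, "Target genes and biomarkers identified as possibly relevant by the latest international research will be tested", and those that differ between rupture and non-rupture groups count as rupture-related.
- **Statistical analysis of clinical data:** one-way ANOVA for continuous variables, Mann–Whitney for skewed ones, and "Categorical variables will be expressed as quantity (rate) and compared using χ^2^ tests". The threshold is "P < 0.05 will denote a significant difference".
- **Evaluation of risk factors for aneurysms:** multiple regression gives odds ratios, the model is assessed in the validation group, and it is then adjusted before being finalised.
- **Total sample size:** at least 130 ruptures are expected in the modeling group in four years. Genes and biomarkers are to be chosen later as research progresses.

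**The concern.** Choosing predictors because they differ significantly, and then estimating their effects in the same data, has three known effects. A factor that passes does so partly because its estimate happened to be large, so its coefficient is biased away from zero. Factors with no effect pass at the rate of the threshold. Real factors with moderate effects can fail to pass. The resulting model looks better in its own data than in new patients, and its predicted risks are too spread out: high risks too high, low risks too low.

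This matters because the Abstract intends the model as a preliminary basis for treating aneurysms at high risk. A model that ranks patients adequately but overstates high risks would mislead in that use.

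**Working it through.** **1. Reproduce the event count.** Inputs: 5000 patients (Abstract), 2:1 split and 1% annual rupture (Design), four years.

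- 5000 × 2/3 × 4 × 0.01 = 133.3, which agrees with at least 130. It assumes four full years for everyone and no loss.
- With the article's 20% loss: 133.3 × 0.8 = 106.7, about 107.
- The 500 for CIAP-2 fits a 1:2 nested set: 130 × 3 = 390, and 390 / 0.8 = 487.5.

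**2. Count the candidates.**

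- Model building: 10 clinical + 6 imaging + 1 wall enhancement + 4 hemodynamic = 21.
- Data collection and management adds 5 (neck size, dome-to-neck ratio, dome-to-artery ratio, presentation, number of aneurysms), giving 26 with some overlap.
- Genes and biomarkers: number not fixed. I assume 50 for illustration, giving 76.

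**3. Events per candidate.**

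| Ruptures | 21 candidates | 26 | 76 |
|---|---|---|---|
| 130 | 6.2 | 5.0 | 1.7 |
| 107 | 5.1 | 4.1 | 1.4 |

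**4. Chance entries.** If all k factors were null and independent, P(at least one passes) = 1 − 0.95^k: 66% for 21, 74% for 26, 98% for 76. If six factors are real, expected false entries are 20 × 0.05 = 1.0 with 26 candidates and 70 × 0.05 = 3.5 with 76.

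**5. Simulation of the screen.** 130 ruptures and 260 non-ruptures; independent normal factors; six real, each with the same assumed odds ratio per SD; t-test at P < 0.05, then logistic regression on the factors that pass; new data of 1000 and 2000; 200 replicates.

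| Candidates, odds ratio | Real factors kept (of 6) | False entries | Inflation of kept log odds ratios | AUC, own data → new data | Slope in new data |
|---|---|---|---|---|---|
| 26, 1.3 | 4.0 | 0.97 | ×1.26 | 0.689 → 0.631 | 0.67 |
| 26, 1.5 | 5.8 | 1.08 | ×1.06 | 0.775 → 0.741 | 0.84 |
| 76, 1.3 | 4.0 | 3.48 | ×1.24 | 0.715 → 0.613 | 0.50 |
| 76, 1.5 | 5.8 | 3.37 | ×1.04 | 0.786 → 0.727 | 0.74 |

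A separate simulation at 130 ruptures and 1:2 sampling, again with assumed effects, gave slopes of about 0.79 to 0.88 with 21 to 26 candidates and 0.60 to 0.72 with 76. Together the ranges are 0.67 to 0.88 and 0.50 to 0.74.

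**6. Cross-check without simulation.** Expected shrinkage S when all p candidates are fitted solves n = p / [(S − 1) ln(1 − R²/S)], where R² is the Nagelkerke value times its maximum. With one third ruptures that maximum is 0.720. For n = 390 and p = 26, S is 0.64 at an assumed Nagelkerke R² of 0.15 and 0.79 at 0.30. Reaching S = 0.90 would need about 2034 and 948 subjects respectively.

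**7. Does the alternative help?** In the separate simulation, ridge regression with a cross-validated penalty gave slopes of about 1.0 to 1.15 with 21 to 26 candidates and 1.14 to 1.17 with 76. It did not raise the AUC, and it lowered it with 76 candidates.

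**The case against.** **The rule is assembled.** No single sentence fixes a P < 0.05 univariable screen for every factor. The tests and threshold sit in a general paragraph on clinical data, the section on risk factors names multiple regression, and the Abstract does not say whether significance is univariable or multivariable. This stands as a limit on the wording. It does not remove the point: the Abstract does tie entry of clinical features to significance, Design and Model building bring in the other factors through group differences, and no other route is given. Significance judged inside the regression would still be selection on the same data.

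**An unseen analysis plan may hold the details.** The lack of any mention of shrinkage is therefore not the finding. The finding is the entry route that the article does state.

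**A validation third is planned, with blind verification.** This is a real strength: optimism in the modeling data would be exposed. But exposure is not correction. The model is then adjusted, so the adjusted version has no untouched data to be checked in.

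**Genes and biomarkers are largely previously reported targets.** That lowers the share with no effect, but the number remains open.

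**Stronger readings.** A reader might infer that the model is bound to be badly overfitted. For example, 60 ruptures with 50 candidates gives a simulated slope of 0.38, and a plain cohort of 500 has only 500 × 2/3 × 4 × 0.01 = 13.3 modeling-group ruptures. The documents do not support either as the main case. The stated count is at least 130, the 500 fits a 1:2 nested set, and 50 is not a number in the article. Staggered entry would reduce the 130, but that is a separate question, and I keep 130 as the favourable case. A reader might also infer that established factors will be dropped. No passage says so; it is only a possible consequence of the rule.

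**Conclusion.** The point holds as a matter of degree. At the article's own 130 ruptures and 21 to 26 named candidates, selection by significance lets in about one chance predictor. It inflates the retained effects by about 6% to 26% on the log-odds scale and gives a new-data calibration slope of roughly 0.67 to 0.88. With 50 added markers (assumed), about three chance predictors enter and the slope falls to 0.50 to 0.74. With strong effects and the named candidates only, the harm is modest; with weak effects or many markers it is material.

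These figures rest on assumed effect sizes, independent normally distributed factors, six real effects in the tabulated runs, and the full 130 ruptures. The direction was the same in every scenario run; the size is not known in advance. The point should be corrected before the model is built, but it does not invalidate the study.

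**What to change.** 1. Remove statistical significance as the condition for entering the model, in the Abstract, Design and Model building alike.
2. Pre-specify a short candidate list. Keep in, whatever their P values, the factors that the Background section on clinical factors treats as predominant or as having an obvious effect (smoking, sex, blood pressure, size, location), plus age. Add wall enhancement and a few hemodynamic indices.
3. Fit by penalised regression with the penalty tuned by cross-validation, using a likelihood or weights that respect the 1:2 rupture to non-rupture sampling. An unweighted cohort model would not.
4. Assess genes and biomarkers as a separate added block, judged by the gain in cross-validated performance.
5. Repeat every selection and tuning step within the internal validation. If the model is adjusted after the validation third has been used, say that this version has not been independently validated.

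The cost is analysis-plan wording, some programming, and coefficients slightly less simple to present. The gain to expect is better-calibrated risks; the simulations give no reason to promise a higher AUC, and they favour keeping the list short.

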**Fig. 2 Fig2:**
[figure not shown]
Flow chart showing development of multidimensional model for prediction bleeding from previously unruptured aneurysms. *MRI* magnetic resonance imaging

### Recruitment of participants

Inclusion criteriaAt least one UIA that has not been treated and has been confirmed by imaging: computed tomography angiography (CTA), magnetic resonance angiography (MRA), and/or digital subtraction angiography (DSA).The ability to live independently and a modified ranking score ≤ 3.Older than 14 years.Patient or relatives have given written informed consent.

Exclusion criteriaSubarachnoid hemorrhage of unknown origin.Presence of other intracranial vascular malformations, such as a cerebral arteriovenous malformation (AVM) or cerebral arteriovenous fistula (AVF).Intracranial and other malignant aneurysms.Traumatic, bacterial, or dissecting aneurysm.Presence of severe mental illness preventing communication.Presence of other diseases or poor general condition with expected survival of less than 1 year.Participant in another similar research program.Refusal to attend for follow-up.

### Data collection and management

The following patient characteristics will be collected and recorded: (1) basic clinical characteristics; (2) relevant data concerning personal and family history; (3) relevant imaging findings; (4) findings of head HRMRI, computational fluid dynamics (CFD) testing, and relevant genetic testing; (5) relevant laboratory findings; and (6) neurological function-related scores on admission or first visit. The following characteristics of aneurysms will be collected and recorded: size, neck size, dome-to-neck ratio, dome-to-artery ratio, shape, location, clinical presentation, and number of aneurysms.

The follow-up data collected will comprise: (1) frequency and number of follow-up assessments; (2) findings on general evaluation; (3) deaths; (4) imaging findings; (5) UIA growth (assessed by repeated imaging to avoid treatment bias); and (6) life-style changes. Throughout, neurobehavioral-related scores will include: (1) Glasgow Coma Scale scores; (2) improved RANKIN scale scores (somatic changes); and (3) Mini-Mental State Examination scores (psychological changes).

The participants will initially be followed up three times: at 90 ± 14 days, 180 ± 30 days, and 365 ± 30 days and at least annually for a minimum of 5 years thereafter. Participation in the study will end if rupture occurs. Patients with SAH will be transferred to the CIAP-5 project (a study of emergency treatment of aneurysmal subarachnoid hemorrhage; CIAP-5, the fifth project of the China Intracranial Aneurysm Project, is managed by Xuanwu Hospital, Capital Medical University, Beijing, China). In addition, patient’s relatives are requested to report sudden deaths to the study group. In such instances, autopsies will immediately be organized in study hospitals and tissue samples of ruptured aneurysms will be supplied to the project for analysis, subject to the informed consent of the participants’ relatives.

Formal training, including investigator training and familiarization with the study protocol, will be initiated. An inspection team of experts drawn from various organizations will follow participants up with the specified regular monitoring until the end of the study period. All data will be collected on paper Case Report Forms (CRF), then input into Electronic Data Capture (EDC) for management, and retained for 5 years after the end of the study. The accuracy and rigorousness of the data will be checked in a timely manner.

This study will incorporate nested screening of 500 individuals from cohort 1 (CIAP-1). Recruitment for this study started in September 2016. The estimated primary completion date will be in December 2020. The project will produce preliminary results in the 5th year. After the end of the 5th year, we will have a longer follow-up visit to the patients who have been in the group.

### Model building (first set of UIA queues)

The following possible or established risk factors for UIA will be collected and analyzed: age; sex; blood pressure, smoking, alcohol consumption, hyperlipidemia, diabetes mellitus, and family history of subarachnoid hemorrhage, intracranial aneurysm, and autosomal dominant diseases (polycystic kidney, Marfan syndrome, collagen dysplasia, etc.)The following imaging data will be collected and analyzed: shape, location, size, aspect ratio and odds ratio of aneurysms, morphological factors such as the angle of the aneurysm jet, and known risk factors for rupture.In our experience, follow-up angiography alone does not adequately predict the outcome whereas HRMRI is a more useful means of following these lesions [38]. We have also found and reported that aneurysm wall enhancement on HRMRI predicts instability of an intracranial aneurysm [39]. HRMRI will be performed on patients enrolled in the UIA follow-up cohort at the 20 participating centers and HRMRI-identified aneurysm wall enhancement assessed as a possible predictor of UIA rupture. Two-dimensional short-axis images of the aneurysms generated from the registered pre-and post-contrast T1w-SPACE images will be used to identify wall enhancement [13].To identify risk factors, the nested cohort study will incorporate the following: incidence of aneurysm rupture in the follow-up cohort, the definition of UIA recently rupture before the duration of follow-up was high risk of rupture of UIA, acquisition of imaging data for hemodynamic calculations; according to the aneurysm ratio of 1:2 UIA (rupture vs non-rupture), and analysis of differences in hemodynamic variables, genetic factors, and biomarkers.A.Analysis of hemodynamic variables: A three-dimensional shape will be created and image data from computed tomographic angiography, magnetic resonance angiography, or DSA saved as DICOM files. Once the 3D model has been reconstructed, it will be saved in an STL file format. A rigid wall in the parent vessel and aneurysm will be assumed in the simulation of hemodynamics. We will start by using ANSYS ICEM CFD (Materialise, Leuven, Belgium) to build a finite element model, then perform a simulation on ANSYS CFX software (Materialise), and finally use ANSYS CFX POST postprocessing to calculate Wall Shear Stress (WSS), maximum wall shear stress (WSSmax), low WSS areas, steady state of blood flow, and so on. Our team has already identified that these factors are associated with the stability of aneurysms [40–42].B.Gene and biomarker analysis: Blood samples will be collected from all participants and specimens of the aneurysm wall from patients who undergo craniotomy. Target chromosomes will be tested for blindly. Target genes and biomarkers identified as possibly relevant by the latest international research will be tested. Differences in genes and biomarkers between rupture and non-rupture groups will be compared to identify rupture-related factors.
Risk factors for rupture, including hemodynamic variables, genes, and biomarkers will be calculated in a nested cohort study of the entire first cohort (CIAP-1: the first project of the China Intracranial Aneurysm Project and is managed by Tangdu Hospital, Fourth Military Medical University). A multi-dimensional model for predicting UIA rupture and bleeding that incorporates clinical, imaging, HRMRI data, and so on will be constructed by using a statistical model.Model validation: After establishment of the model, the second group of the follow-up cohort will be used for blind verification.Comparative analyses of histopathology of aneurysm walls: When participants undergo surgery for ruptured intracranial aneurysms, the sites of rupture will be identified intraoperatively and specimens of the aneurysm wall will be removed and preserved in formalin. The location of rupture, pathological damage, hemodynamic variables, HRMRI findings, and relevant biomarkers will be analyzed to identify differences between unruptured and unruptured aneurysms. Relationships between pathological damage, hemodynamic variables, and HRMRI features of the aneurysm wall will also be assessed.

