
## Methods and design

The Study on a Multidimensional Model for Predicting Risk of Rupture of Unruptured Intracranial Aneurysms (CIAP-2) is the second project of the China Intracranial Aneurysm Program and is managed by Beijing Neurosurgical Institute and Beijing Tiantan Hospital), which manages a prospective observational registry of patients with UIA who were enrolled in our 20 centers in China during the first CIAP. It is sponsored by the National Key Research Development Program of China. This study has been designed as a prospective, observational registry and the treatment of patients will not be influenced by their participation in this observational study. This study adheres to the ethical principles of the Declaration of Helsinki and Human Biomedical Research Ethical Issues and Policy Guidance. The Institutional Review Board of Beijing Tiantan Hospital, Capital Medical University has approved the study (KY2017-017-01). We will inform participating patients or their relatives that the privacy of their data will be protected. These know they can withdraw from the study at any time. The study has been registered at https://clinicaltrials.gov/ct2/show/NCT03133624.

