## Statistical methods

### Total sample size

CIAP-1: Calculation of the required sample size using an expected annual rupture rate of 1%, allowable error of d = 0.6%, and alpha = 0.05 on two-sided testing indicated that 1173 patients need to be enrolled per year, that is, 4692 over 4 years. An annual rupture rate of 1% [2] results in a loss rate of less than 20%. A reported hemodynamic index (complex flow patterns OR = 4.7) and HRMRI index (aneurysmal wall enhancement OR = 3.05 for ruptured versus unruptured aneurysm) also indicate that this sample size would be sufficient [12, 43]. Given that genetic factors have not yet been evaluated [35], our genetic testing will assess previously reported possible genetic indicators of prognosis; additionally, target genes and biomarkers will be selected according to the latest research progress in the future. In the 5th year of the study, we will analyze the data. As previously mentioned, at least 130 aneurysms are expected to rupture in the modeling group in the first 4 years. Allowing for a loss rate of 20%, the study will need to enroll 500 individuals.

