### Expected loss rate (less than 20%)

The expected loss includes all patient data excluded from the main analysis, usually because of a serious breach of the study protocol by the principal investigator (affecting the evaluation of the primary endpoint of effectiveness). Possible such breaches include failure to meet the inclusion/exclusion criteria; failure to follow the prescribed schedule; follow-up visits not occurring within the specified time limits, and concomitant treatments that may affect incidence of rupture. However, excellent clinical follow-up may achieve a drop-out rate of as little as 5%.

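### Non-rupture controls need not be unrepaired and under follow-up when their case ruptures, and the treatment exclusion is not tied to them; if repair depends on a predictor, its odds ratio is biased in either direction

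*Protocol article*

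**What the plan says.** All places are in the protocol article.

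- **Model building:** the nested comparison is formed "according to the aneurysm ratio of 1:2 UIA (rupture vs non-rupture", for hemodynamic variables, genetic factors and biomarkers. Nothing is said about a control's repair status or follow-up time when its case ruptured.
- **Design; Evaluation of risk factors for aneurysms:** the modeling group is split into rupture and non-rupture to compare clinical, radiological and HRMRI factors as well, and the risk factors are reported as odds ratios.
- **Recruitment of participants; Methods and design:** patients enter with an untreated aneurysm, and thereafter "the treatment of patients will not be influenced by their participation in this observational study". They also know that "they can withdraw from the study at any time".
- **Data collection and management:** "Participation in the study will end if rupture occurs". The itemised follow-up data include neither repair nor its date, and no censoring at repair is stated.
- **Expected loss rate:** "The expected loss includes all patient data excluded from the main analysis", and one of the listed reasons is "concomitant treatments that may affect incidence of rupture". The text does not say whether clipping or coiling is meant, and control selection does not refer to it.
- **Model building, gene and biomarker item:** tissue is to come as "specimens of the aneurysm wall from patients who undergo craniotomy".

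**The concern.** A repaired aneurysm is no longer at risk in the same way as an untreated one. If it stays in the pool, it counts as non-rupture for a reason unrelated to its natural course. If it is removed entirely, the time it spent at risk without rupturing before repair is thrown away. Either is harmless when repair has nothing to do with the predictors.

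Repair may well be selective here. The Background calls it inappropriate to recommend treatment for all small aneurysms, so treatment is expected to vary with size, which is one of the candidate predictors. Under Data collection and management, treatment bias is guarded against for aneurysm growth only, not for rupture.

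At stake are the odds ratios that go into the prediction model. The Abstract intends that model as a preliminary basis for treating aneurysms at high risk. The features most likely to prompt repair would be the ones most distorted, and the reader could not tell in which direction.

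**Working it through.** **The plan's own figure.** 130 ruptures with two controls each give 130 × 3 = 390 aneurysms. Allowing for 20% loss, 390 / 0.8 = 488, close to the stated 500. The article does not spell this derivation out, but its figures are consistent with the 1:2 sampling being the basis of the 500.

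**Inputs from the document.** Rupture 1% per year on average; 4 years; "aneurysmal wall enhancement OR = 3.05 for ruptured versus unruptured aneurysm"; and an odds ratio of 4.7 for complex flow patterns (Total sample size). The two ratios are used here as rupture hazard ratios.

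**Assumed inputs.** Feature prevalence 30%; constant hazards of rupture and repair; the repair rates in the table. The document gives none of these.

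**Formulas.** With rupture hazard r and repair hazard t, over 4 years:

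- Probability of observed rupture: F = r/(r+t) × [1 − exp(−4(r+t))]
- Probability of being neither ruptured nor repaired: S = exp(−4(r+t))
- Repaired kept as non-rupture: OR = [F1/(1−F1)] / [F0/(1−F0)]
- Repaired excluded: OR = [F1/S1] / [F0/S0]

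Subscript 1 means feature present and 0 means absent. Drawing controls at random from the non-rupture group leaves these expected ratios unchanged, so they apply to the 1:2 sample and to the cohort-wide comparison alike.

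**Worked case: ratio 3.05, repair 5% vs 10% per year.**

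- r0 = 0.01 / (0.7 + 0.3 × 3.05) = 0.00619; r1 = 3.05 × r0 = 0.01889
- F1 = 0.06012, S1 = 0.62155; F0 = 0.02218, S0 = 0.79870
- Kept: (0.06012/0.93988) / (0.02218/0.97782) = 2.82
- Excluded: (0.06012/0.62155) / (0.02218/0.79870) = 3.48

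With no repair the 4-year odds ratio is 3.13, slightly above 3.05 because an odds ratio over 4 years exceeds the hazard ratio. Relative to 3.13, the two readings are about 10% low (2.82/3.13 = 0.90) and 11% high (3.48/3.13 = 1.11).

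| Repair per year, feature absent vs present | 3.05: kept | 3.05: excluded | 4.7: kept | 4.7: excluded |
|---|---|---|---|---|
| none | 3.13 | 3.13 | 4.87 | 4.87 |
| 5% vs 5% | 3.12 | 3.13 | 4.84 | 4.87 |
| 5% vs 10% | 2.82 | 3.48 | 4.38 | 5.42 |
| 5% vs 20% | 2.34 | 4.35 | 3.62 | 6.78 |
| 10% vs 30% | 2.16 | 4.95 | 3.35 | 7.72 |
| 10% vs 50% | 1.60 | 8.22 | 2.47 | 12.82 |

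Changing the prevalence to 20% or 40% moves the worked case only to 2.83 or 2.81 (kept) and 3.50 or 3.47 (excluded). The last rows are extreme and mark the edge of the range. Controls sampled among aneurysms still unrepaired when the case ruptures target the hazard ratio itself, 3.05 or 4.7, under these assumptions.

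**The case against.** **Rupture is not the only stated exit.** A reader might infer that it is, and hence that every repaired aneurysm becomes a control. The document does not support that: patients may withdraw, and the loss section removes data for treatments that may affect rupture, of which clipping or coiling is a natural example. This stands, and it means the bias cannot be assumed to run toward 1. It does not clear the plan, because excluding patients for a treatment given after enrolment that may depend on the predictors is itself a source of bias. That section also lists such treatment as a protocol breach, although treatment is otherwise left to usual care.

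**The 1:2 sampling has a limited scope.** It names hemodynamics, genes and biomarkers, not size or shape, and the document does not suggest that usual care selects repair on genes or biomarkers. This stands for the nested sample, and for any factor unrelated to repair there is almost no bias. Clinical, imaging and HRMRI factors meet the same problem through the cohort-wide rupture versus non-rupture comparison.

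**The evidence on repair is thin.** The craniotomy specimens may come from ruptured aneurysms, since the histopathology item describes surgery after rupture. No repair frequency is given. CIAP-4 handles the comparison of treatments, and the flow charts, which might show how treated patients move between projects, are not reproduced. This stands as a limit on the size. Usual-care treatment of patients who enter with an untreated aneurysm is still enough to make repair during follow-up foreseeable.

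**An article leaves detail to the full protocol.** That is fair for procedural detail. But the article does state a control rule and a treatment exclusion, and as stated the two are not reconciled.

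**Conclusion.** The point holds in a two-directional form. As written, the control group is not restricted to aneurysms still at risk when the case ruptured, and the treatment exclusion neither says whether repair is covered nor reaches control selection. If repair depends on a predictor, one reading understates its odds ratio and the other overstates it. A claim that the strongest risk factors are necessarily pulled toward 1 goes further than the document allows.

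The size cannot be determined from the document. At the mildest unequal rates considered (5% vs 10% per year) the distortion is about 10% either way, and it grows as repair becomes more selective. It all but vanishes when repair is unrelated to the predictor. These figures rest on constant hazards, the assumed repair rates and prevalence, and the reading of 3.05 and 4.7 as rupture hazard ratios. The change is worth making because it is inexpensive and resolves both readings.

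**What to change.** - **Data collection and management:** record the date of repair for each aneurysm, and state that its time at risk ends at repair, withdrawal or loss to follow-up.
- **Model building:** for each rupture, sample two controls from aneurysms that are unruptured, unrepaired and under follow-up at the same time since enrolment. An aneurysm repaired later may be a control only for ruptures before its repair. Use predictor values from enrolment, or from the same scheduled visit where they are already collected; no repeat blood sampling is listed, so none should be required.
- **Expected loss rate:** replace any exclusion of repaired patients by censoring at repair, so that their earlier time at risk counts.
- **Evaluation of risk factors:** apply the same time at risk to the cohort-wide comparison of clinical, imaging and HRMRI factors.

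Cost: one date field and a few sentences. The 1:2 ratio and the number of assays do not change, and no treatment decision is affected. Slightly fewer controls are eligible late in follow-up, which matters little when non-ruptures far outnumber ruptures. Censoring at repair still assumes that, given the predictors in the model, repair carries no further information about rupture risk; the plan should state that assumption.
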